### Interventionists

Two interventionists will lead the MBI groups - one in Porto Alegre and one in São Paulo. Both have been certified by Mente Aberta - Brazilian Center for Mindfulness and Health Promotion to teach mindfulness courses. This rigorous training follows the British and Brazilian guidelines for good practices of mindfulness [44, 45]. An independent experienced mindfulness teacher will assess intervention fidelity using video recordings of the sessions.

### Intervention

The intervention in the POLICE study will be the Mindfulness-Based Health Promotion (MBHP) program [46]. MBHP is an 8-week MBI developed by our research group (see Table 1), based on the Mindfulness-Based Stress Reduction (MBSR) model created by Jon Kabat-Zinn and colleagues [47]. We adapted the MBSR model in order to suit the context and needs of primary health care and national and local health systems, developing a framework that supports the learning process to individuals from distinctive cultural and educational backgrounds. MBHP was designed to address human universal vulnerabilities, not focusing in any specific health condition. It has been applied over the last years by Mente Aberta - Brazilian Center for Mindfulness and Health Promotion [48], and by the University of Zaragoza, in Spain [49]. There is a strong emphasis on informal mindfulness practices, such as walking, eating, exercising, talking and doing housework. Concepts of radical acceptance [50], values clarification [51] and positive psychology [52] are also heavily emphasized. Compassion training techniques are also included in the program (equanimity in the condition of human suffering, receiving affection and showing affection to oneself), which can be particularly useful for persons high on guilt or self-criticism like police officers.

**Table 1 Tab1:** Mindfulness-Based Health Promotion content

Session	Didactive teaching	Practices	Homework
1. What is mindfulness	-Presentation and aims-Stress and dispersion-What is and what isn’t mindfulness-Characteristics, attitudes and motivation-Introduction to practice diaries	-Eating a raisin-Simple mindfulness exercises (listening to sounds, areas of contact with your body, the feel of your feet touching the floor)-Body scan-9-dots exercise	-Body scan-Attention for routine activity-Eating one meal mindfully-Mindfulness diary
2. Mindfulness in breathing	-What to do with the body-What to do with the mind-Breathing-Information on posture-Preconceptions/fears/challenges in meditation	-Mindfulness in breathing-Body scan-Primary and secondary suffering	-Body scan-Mindfulness in breathing-Awareness of pleasant events (diary)-Attention for routine activity-Habit changing
3. Mindfulness in the body (part I)	-Importance of the body-How mindfulness works-Cognitive defusion	-Mindful walking-Mindfulness in breathing-Hello, thank you and goodbye	-Body scan-Mindfulness in breathing-Mindful walking-Awareness of unpleasant events (diary)-Attention for routine walking
4. Mindfulness in the body (part II)	-Doing mode/being mode-Reinforcing daily practice-Obstacles to the practice-Self -compassion	-Mindful movements -Mindfulness in breathing, sensations, sounds and thoughts-3-min breathing space-Mindful walking	-Body scan-Mindfulness in breathing-Mindful walking-3-min breathing space-Awareness of communication difficulties (diary)
5. Mindfulness, acceptance and values	-Importance of acceptance-Values and committed action-Meaning of life-Hedonic and eudaimonic well-being	-Mindful movements-Mindfulness of thoughts-3-min breathing space in doubles	-Practice of choice-3-min breathing space during stress
6. Silence		-Mindful movements-Body scan-Sitting meditation-Mindful walking	-Practice of choice-Mindfulness conversation
7. Compassion	-What is and what isn’t compassion-Biological basis-Ways of training compassion-Fear of compassion in western society	-Loving-kindness (for oneself and others)-Sitting meditation-Mindful movements	-Practice of choice- Loving-kindness (for oneself and others)-Attention for self-compassion in routine activity
8. Mindfulness for life	-Mindfulness in daily life-Recommendation for long-term practice	-Loving-kindness (for oneself and others)-Mindfulness poetry	-Daily life mindfulness incorporation

### Assessments and outcomes

The three assessment points—baseline, post-intervention and follow-up—will occur over the two weeks preceding the intervention, the two weeks after the intervention, and six months after the intervention, respectively (see Table 2). The baseline assessment also will include sociodemographic and clinical characteristics. Survey Monkey Software [53] will be used for data collection. During research visits the participants will enter responses directly into the electronic system. Whenever this may not be possible, the research team will provide sheets of paper and the answers will be uploaded by the team. All instruments have been translated to Portuguese with reliable psychometric properties [54–64].

**Table 2 Tab2:** Assessments as a function of time points (according to 2013 SPIRIT figure guidelines)

Measure	Target	T0	T1	T2
		Baseline	Post-intervention (8 weeks)	Follow-up (6 months)
*MINI*	Psychiatry disorders	x		
*WHOQOL-BREF*	Quality of life	x	x	X
*MBI-GS*	Burnout symptoms	x	x	X
*PSQ*	Stress	x	x	X
*HADS*	Anxiety and depression symptoms	x	x	X
*CD-RISC-25*	Resilience	x	x	X
*MAAS*	Mindfulness trait	x	x	X
*EQ*	Decentering	x	x	X
*SCS*	Self-compassion	x	x	X
*GHQ-12*	Mental well-being	x	x	X
*BCSQ-12*	Burnout subtypes	x	x	X
*WHOQOL-SRPB-BREF*	Spirituality, religiosity and personal beliefs	x	x	X
*DUREL*	Religiosity	x	x	X

*MINI* Mini International Neuropsychiatric Interview, *WHOQOL-BREF* World Health Organization Quality of Life bref, *MBI-GS* Maslach Burnout Inventory - General Survey, *PSQ* Police Stress Questionnaire, *HADS* Hospital Anxiety and Depression Scale, *CD-RISC-25* Connor-Davidson-25 Scale of Resilience, *MAAS* Mindful Attention Awareness Scale, *EQ* Experience Questionnaire, *SCS* Self Compassion Scale, *GHQ-12* The 12-Item General Health Questionnaire, *BCSQ-12* Burnout Clinical Subtype Questionnaire, *WHOQOL-SRPB-BREF* World Health Organization Quality of Life Bref -Spirituality, Religiousness and Personal Beliefs, *DUREL* Duke University Religion Index

### Diagnostic interview

The Mini International Neuropsychiatric Interview (MINI) is a short, structured diagnostic interview that is used for the diagnosis of DSM-IV and ICD-10 psychiatric disorders. With an administration time of approximately 15 min, the MINI was designed to provide a short but accurate structured psychiatric interview for multicentric clinical trials and epidemiology studies [43].

### Primary outcomes measures

*World Health Organization Quality of Life- BREF (WHOQOL-BREF):* the World Health Organization has developed a quality of life instrument, the WHOQOL, which captures many subjective aspects of quality of life. The WHOQOL-BREF is a WHOQOL shorter version, comprises 26 items that produces scores for four domains related to quality of life: physical health, psychological, social relationships and environment. It also includes one facet on overall quality of life and general health. Is one of the best known instruments that has been developed for cross-cultural comparisons of quality of life and is available in more than 40 languages [65]. Evidence consistently shows that officers exhibit low quality of life and its correlation with adverse mental health outcomes [4, 66, 67].*Maslach Burnout Inventory - General Survey (MBI-GS):* is considered one of the leading measures of burnout. Validated by extensive research, MBI-GS Surveys address three dimensions: Emotional Exhaustion measures feelings of being emotionally overextended and exhausted by one’s work; Depersonalization measures an unfeeling and impersonal response toward recipients of one’s service, care treatment, or instruction; Personal Accomplishment measures feelings of competence and successful achievement in one’s work. The MBI-GS is designed for use with occupational groups. The 3 dimensions are distributed in 16 items, whose answers are given on a 7-point Likert scale that varies from “never” to “every day” [68]. Nature and environment of police work contributes to high burnout rates which are associated with escalating symptoms of diminished health [22].

### Secondary outcomes measures

*Police Stress Questionnaire (PSQ) -* stress will be measured using the PSQ, a 40-item psychometric questionnaire consisting of two subscales that measure organizational and operational stressors in the context of police work, using 7-point scales (Likert type) ranging from 1 (absence of stress) to 7 extreme stress). The PSQ was developed as an alternative to the general scales of stress at work in order to reflect the specifics stressors of police occupation [69].*Hospital Anxiety and Depression Scale (HADS)* - is a 14-item questionnaire with seven items measuring anxiety (HAD-A) and seven measuring depression (HAD-D). The ratings are totaled to obtain a score ranging from 0 to 21 for anxiety and depression, with higher scores indicating greater depression or anxiety. Scores between 8 and 10 represent possible cases of anxiety or depression, and scores that are ≥11 correspond to probable cases [70].*Connor-Davidson-25 Scale of Resilience (CD-RISC-25)*: it assesses the ability of individuals to cope and adapt physically, mentally, and spiritually to the circumstances imposed by life. CD-RISC-25 is composed of 25 items on a Likert scale (0–4), with larger scores reflecting greater resilience. Resilience may be viewed as a measure of stress coping ability and, as such, could be an important target of treatment in anxiety, depression, and stress reactions [71].*Mindful Attention Awareness Scale (MAAS)*: is a 15-item scale designed to assess a core characteristic of dispositional mindfulness, namely, open or receptive awareness of and attention to what is occurring in the present. The scale has strong psychometric properties and has been validated with college, community, and cancer patient samples [72].*Experience Questionnaire (EQ)*: this instrument was designed to measure the capacity to observe one’s thoughts and feelings as temporary and objective events of the mind, also known as “decentering”. Items from the scale are rated on a Likert scale ranging between 1 (never or very rarely true) and 5 (very often or always true), with higher scores indicating greater decentering [73].*Self Compassion Scale (SCS):* is composed by 26 items measuring six components of self-compassion: self-kindness, self-judgment, common humanity, isolation, mindfulness and over-identification.The items are rated on a five-point response scale ranging from 1 (almost never) to 5 (almost always) [74].*The 12-Item General Health Questionnaire (GHQ-12)*: is the most extensively used screening instrument for common mental disorders, in addition to being a more general measure of mental well-being. It consists of 12 items, whose answers are given on a 4-point Likert scale [75].*Burnout Clinical Subtype Questionnaire (BCSQ-12):* it aims to evaluate the most important clinical subtypes of burnout, comprising the dimensions of overload, lack of development and neglect. Consists of 12 items distributed in 3 dimensions, whose answers are given on a 7-point Likert scale ranging from “totally agree” to “totally disagree” [76].*WHOQOL-SRPB-BREF*: this scale measures the domains of spirituality, religiosity and personal beliefs in the quality of life from a cross-cultural perspective. Combines one item extracted from each of the eight SRPB facets in the WHOQOL-SRPB, with the 26 WHOQOL-BREF items, extracted from the WHOQOL-100, to construct the 34 item WHOQOL-SRPB-BREF [77].*Duke University Religion Index (DUREL)*: scale of religiousness developed by Duke University, 5 items are used to evaluate religious involvement. It captures the three dimensions of religiosity that most correlate with health outcomes: organizational religiosity, non-organizational religiosity, and intrinsic religiosity (or subjective religiosity) [78].

To explore the feasibility and adherence of MBHP among police officers, the frequency of attendance to the sessions will be assessed. At the post-intervention and the six-month follow-up evaluations we will address mindfulness practice parameters such as type, frequency and length of personal meditative practice through a questionnaire created by our research group [79].

### Statistical analysis

Intention-to-treat (ITT) and per protocol analyses (PPA) will be conducted following the CONSORT recommendations for reporting the results [41]. Baseline differences between groups on sociodemographic and clinical variables will be assessed using Chi-square tests for categorical variables and analysis of variance (ANOVA) for continuous data. A 2 (Group: MBI vs. WL) × 3 (Time: baseline, post, and 6-month follow-up) repeated measures ANOVA will be conducted to test the effects of the intervention for all primary and secondary outcomes. Effect sizes (Cohen’s *d*) and confidence intervals for within- and between-group comparisons will be performed for each study outcome. Missing data will be handled according to the most appropriate method depending on the reasons for missingness, following the authors’ recommendations and sensitivity analyses principles [80].

To study potential working mechanisms of mindfulness intervention, mediation analysis will be conducted using the Preacher and Hayes (2004) procedure [81]. The mediation effects of mindfulness, self-compassion, resilience, decentering and spirituality on burnout symptoms and quality of life will be evaluated.

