### Sample size and power calculations

Power calculations were conducted to determinate the required sample size for the primary outcomes using the statistical software G * Power 3.1.9.2. The minimum sample for each group was identified as 64 to detect a moderate effect size of 0.5 (Cohen’s *d*) with a power of .80 and an alpha of 0.05, based on a previous study [42]. Therefore, the RCT will enroll 160 participants (80 each group) and allow for up to 20% loss to follow-up, expecting a minimum effective sample size of 128 individuals.

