### Participants and settings

Two types of police officers will be recruited for the POLICE study in two Brazilian metropolitan areas:*Civil Police.* The study center in Porto Alegre will be located in the Police Hall of the State of Rio Grande do Sul. Civil Police main duties are to oversee public order and security, adopt measures necessary to avoid danger or injury to persons and public or private property, ensure the administration of criminal offenses, including execution of arrest warrants and requisitions requested by the judicial branch.*Civil Guard.* The study center in São Paulo will be located in the headquarters of Unifesp Santo Amaro Campus. Civil Guard fundamental duties include the protection of goods, services and municipal facilities, as well as patrolling areas and preventive policing.

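### The 2 x 3 repeated measures ANOVA that includes baseline is not the two-group comparison that gave 64 per arm; one named, baseline-adjusted between-arm contrast would answer the question directly at no cost

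*Protocol article*

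**What the plan says.** In the protocol article, Statistical analysis, the efficacy test is a two-factor model, group (two levels) by time (baseline, post-intervention, six months): "repeated measures ANOVA will be conducted to test the effects of the intervention for all primary and secondary outcomes". Baseline is therefore one level of the outcome factor. The section does not say whether the group term or the group x time term is the test of efficacy, and it names no visit. It also promises Cohen's d with confidence intervals, within and between groups, for each outcome.

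The section Sample size and power calculations states: "The minimum sample for each group was identified as 64 to detect a moderate effect size of 0.5". The error rates behind that figure are given in the same sentence: "with a power of .80 and an alpha of 0.05". Enrolment is then raised for dropout: "the RCT will enroll 160 participants (80 each group) and allow for up to 20% loss to follow-up". That leaves 128 officers, or 64 per arm, for analysis. The section gives no within-person correlation, no number of repeated measures and no visit.

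Table 2 schedules both primary instruments (WHOQOL-BREF and MBI-GS) at baseline, post-intervention and six months.

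**The concern.** The trial was sized for one test and will be analysed with another. The sample size is for a difference between two group means. The analysis offers two candidate terms, and each has a weakness as a test of efficacy.

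- **Group main effect.** It averages the arm difference over three visits, one of which precedes treatment, so a sustained benefit is estimated at two thirds of its size.
- **Group x time.** It has 2 degrees of freedom and no direction. A small p-value says that the arms' profiles differ, not that mindfulness training helped, nor at which visit.

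The Aims state a directional hypothesis (less burnout, better quality of life), and the Discussion wants to know whether gains last to six months. The meaning of the primary p-value is at stake, and with it whether the stated power of 0.80 applies to the test that will be reported.

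**Working it through.** **Inputs from the article:** d = 0.5, n = 64 per arm after dropout, alpha 0.05, three visits. Sidedness is not stated; two-sided reproduces 64.

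**Assumptions, because the article gives no figure:** equal correlation rho between every pair of visits, shown at 0.3 / 0.5 / 0.7; SD 1 at each visit. The arm differences at the three visits are (0, 0.5, 0.5) if sustained, (0, 0.5, 0.25) if half is lost, and (0, 0.5, 0) if all is lost.

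**1. The plan's own figure.** Two-sample t-test, two-sided: noncentrality 0.5 / sqrt(2/64) = 2.83 on 126 df, power 0.801. Solving for power 0.80 gives 63.77, so 64 per arm. A one-sided test would need 51. Dropout: 64 / 0.80 = 80 per arm, 160 in total. The figure is reproduced, and it is that of a two-group comparison with no repeated measures.

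**2. Group main effect.** Effect (0 + 0.5 + 0.5)/3 = 0.333; variance of a person's three-visit mean (1 + 2rho)/3. At rho 0.5: 0.333 / sqrt(2 x 0.667/64) = 2.31.

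**3. Group x time.** Noncentral F on 2 and 252 df, with lambda = (n/2) x sum of (d_t - mean d)^2 / (1 - rho).
- Sustained: squared deviations 0.1111 + 0.0278 + 0.0278 = 0.1667. At rho 0.5, lambda = 32 x 0.1667 / 0.5 = 10.67. A simulation gave 0.835 against the formula's 0.836.
- All lost: 0.0278 + 0.1111 + 0.0278 = 0.1667. This is the same lambda and so the same power as for a sustained benefit. Reversing every sign (harm) also leaves lambda unchanged.
- Half lost: 0.0625 + 0.0625 + 0 = 0.125; lambda = 8.00 at rho 0.5.

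**4. Baseline-adjusted contrast.** Noncentral t on 125 df. Residual variance is 1 - rho^2 at one visit and (1 + rho)/2 - rho^2 for the mean of the two later visits. At rho 0.5: one visit 0.5 / sqrt(2 x 0.75/64) = 3.27; mean of two 0.5 / sqrt(2 x 0.50/64) = 4.00.

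| Test, 64 per arm | rho 0.3 | rho 0.5 | rho 0.7 |
|---|---|---|---|
| Two-sample t (the sample-size basis) | 0.80 | 0.80 | 0.80 |
| Group main effect, sustained | 0.73 | 0.63 | 0.55 |
| Group x time, sustained or all lost | 0.69 | 0.84 | 0.97 |
| Group x time, half lost | 0.56 | 0.71 | 0.91 |
| Adjusted, one visit with d = 0.5 | 0.84 | 0.90 | 0.98 |
| Adjusted, six months, half lost (d = 0.25) | 0.31 | 0.37 | 0.50 |
| Adjusted, mean of two visits, sustained | 0.96 | 0.98 | 0.997 |
| Adjusted, mean of two visits, half lost (0.375) | 0.80 | 0.85 | 0.94 |

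**5. Site.** With two sites of equal size, an assumed site difference of 0.2 / 0.3 / 0.5 SD takes up 1.0% / 2.3% / 6.3% of the variance (difference squared over 4). Power of a post-only comparison moves from 0.801 to 0.805 / 0.810 / 0.826. In the group x time test a constant site shift cancels within person.

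**The case against.** The strongest defence is that group x time is a valid test in a randomised trial and already uses baseline, because its contrasts include change from baseline. For a sustained benefit its power is above 0.80 from a rho of about 0.5, and at rho 0.8 it equals the single-visit adjusted contrast (0.998 against 0.997). The adjusted contrast is not always stronger: at a visit where the benefit has faded to 0.25 it does worse than the interaction (0.37 against 0.71 at rho 0.5). The article also promises between-group effect sizes with intervals, so directional estimates will be reported. All of this stands. It does not remove the mismatch: the article itself commits every outcome to this ANOVA, and none of the promised effect sizes is tied to a visit or marked as the primary result.

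A reader might infer more, and the documents do not support it:

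- **That the trial is underpowered.** This would need a low rho, a fading effect, or the group term as the test. The article fixes none of these.
- **That missing covariates cause the mismatch.** The t-test behind 64 per group has no covariates either. The cause is the 2-df interaction or the diluted main effect.
- **That leaving out site costs real precision.** The article recruits at two centres ("Two types of police officers will be recruited for the POLICE study in two Brazilian metropolitan areas") with different forces and one teacher each, so a site term is reasonable. The gain in step 5 is small, and the article states no stratification by site.
- **That the baseline tests distort the result.** The plan says "Baseline differences between groups on sociodemographic and clinical variables will be assessed using Chi-square tests". In a randomised trial such tests detect only chance differences, but nothing in the article feeds them into the efficacy test.

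**Conclusion.** The point holds as a mismatch between the test that was sized and the test that is planned, and as a clear opportunity to do better with the same data. The group term falls short of 0.80 at every rho examined (0.73 down to 0.55 for a sustained benefit). The group x time term runs from 0.56 to 0.97 depending on rho and time course. It cannot separate benefit from harm, or a lasting benefit from one lost by six months.

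A baseline-adjusted contrast has power 0.84 to 0.98 at a visit where d = 0.5. For the mean of both later visits it has 0.96 to 0.997 if the benefit is sustained and 0.80 to 0.94 if half is lost. The gain over the interaction for a sustained benefit is largest at low rho and small at 0.7 or more (0.976 against 0.971 for one visit).

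These figures rest on 64 per arm, equal correlations and rho values that the article does not give. The planned ANOVA is not invalid. The change is an improvement in clarity and efficiency, best made before the data are analysed.

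**What to change.** 1. For each primary outcome, name in advance one between-arm contrast: either a stated visit or the mean of the post-intervention and six-month visits.
2. Estimate it from an ANCOVA, or a mixed model of the two post-baseline visits, with the baseline score of that outcome as covariate. Report the arm difference with its 95% confidence interval as the primary result. The other visits and the arm x visit term become supporting results.
3. Choose the contrast with the expected time course in mind, since a single-visit contrast loses power if the effect has faded at that visit.
4. Reword the sample-size section so that d = 0.5 refers to that contrast, and state the correlation assumed if baseline adjustment is counted in the power.
5. Optional: add site as a factor, and describe baseline characteristics by arm without significance tests. The second is reporting practice and changes no efficacy result.

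**Cost:** wording only. The baseline score is already scheduled for every primary and secondary instrument (Table 2), so no extra visits or participants are needed. Recruitment was still under way when the article was submitted (Trial status), which left time to make the change before analysis.
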